## 12. Across All Studies, Other Common Elements Include

Stop-and-go criteria [39] will be used in terms of subject recruitment (<20% vs. >50% meeting eligibility criteria, respectively); intervention acceptability (<30% vs. >60 or >70%, respectively, in different studies), and loss to follow up (<30% vs. >70 or >80%, respectively, in different studies). Furthermore, the RE-AIM framework [61] will be used to guide the evaluation of all studies. We will collect metrics on Reach (e.g., number of website visits), Effectiveness (changes in stay-at-home motivation and intention or changes in hygiene practice), Adoption (e.g., the amount of content created by the public with the campaign hashtag), Implementation (e.g., consistency in implementation of the educational VRG), and Maintenance (e.g., number website visits after the programme) as appropriate, to document formative and summative impact. All analyses will be performed using SPSS 26.0 software and a *p* value < 0.05 will be considered statistically significant.

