#### 8.2.1. Subjects

Phase 1. Thirty EM adults, 30 PWCI and 30 CGs will be recruited for focus group interviews before the development of the interventions begins. Another 10 EM adults (2 from each ethnic group), 10 PWCI and 10 CGs will be invited to participate in cognitive interviews. Phase 2. Twenty EM adults, 20 PWCI, 20 CGs and 6 moderators will be invited to participate. Phase 3. One hundred fifty-six EM adults, 156 PWCI and 156 CGs will be randomised to the intervention or the control group.

We estimated the sample size for the trial of each proposed study based on a previous eHealth Literacy study that reported a small-to-moderate effect size (d = 0.245) [38]. For the proposed study, with five repeated measurements over a 6-month period, a total sample size of 108 subjects (i.e., 54 per group) is required to achieve a power of 90% when using a repeated-measures analysis of variance to detect a significant between-group interaction effect at 5% significance (G*Power 3.1). Furthermore, assuming an attrition rate of 30% [39], 156 subjects (78 per group) will be recruited for each study.

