Stage 2: Participants of stage 2 will be identified from the survey population of study 1. All Hong Kong-resident adults with COVID-19 vaccine hesitancy will be eligible. People with self-reported cognitive impairments or mental disorders that might interfere with their understanding of the intervention content, and those currently engaged in another clinical trial in relation to COVID-19 vaccines, will be excluded. We calculated our sample based on sample size determination methods for repeated measures. Assuming a Type I error rate of 0.05, primary hypothesis of time x intervention interaction, a change of 1.0 as minimum difference in the mean values of the variable, and estimated correlations among repeated measure of the variable as 0.6 for T0–T1, 0.5 for T0–T2, 0.4 for T0–T3, and a statistical power of 80%, as well as 20% attrition rate, the sample size is calculated to be 168 (i.e., 84 for each group) for two study groups. Block randomisation with a size of 6 will be performed with a computer-generated list of numbers known only to an independent administrator.

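### The stop/go criterion for loss to follow-up in Section 12 runs in the wrong direction and contradicts the attrition the protocol plans for

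*Protocol article*

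**What the plan says.** Section 12 of the protocol article, on elements common to all the studies, gives three progression criteria in one sentence. The first is "Stop-and-go criteria [39] will be used in terms of subject recruitment (<20% vs. >50% meeting eligibility criteria, respectively"). The second is "intervention acceptability (<30% vs. >60 or >70%, respectively, in different studies"). The third is "loss to follow up (<30% vs. >70 or >80%, respectively, in different studies").

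Two of the studies state how much attrition they plan for. Study 2 (Section 8.2.1) says that "a total sample size of 108 subjects (i.e., 54 per group) is required to achieve a power of 90" per cent, and then "assuming an attrition rate of 30% [39], 156 subjects (78 per group) will be recruited for each study". Study 4 (Section 10.2.3, Stage 2) gives its size "as well as 20% attrition rate, the sample size is calculated to be 168 (i.e., 84 for each group"). The sample-size paragraphs of Studies 1, 3 and 5 state no attrition allowance.

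Nothing elsewhere in the article redefines the third quantity as retention or reverses the order for it.

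**The concern.** The criteria are named in the order stop, then go, and each pair of values is tied to that order by the word respectively. For eligibility and acceptability this works, because a low percentage is a bad sign and a high one a good sign. The third criterion keeps the order and the inequality signs but names a quantity for which a high percentage is the bad sign. As printed, good follow-up is the reason to stop and heavy loss is the reason to go on.

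This is a stated decision threshold, and it applies across the programme. The article also presents itself as a design that others could adopt in later pandemics, so the rule may be copied as it stands. A progression rule fixed in advance should not depend on the reader noticing that it has to be inverted.

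**Working it through.** The thresholds are stated without a derivation, so there is no formula to reproduce for them. The check sets the three criteria side by side and then compares the third with the protocol's own attrition allowances.

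**Direction, from Section 12**

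| Criterion | Stop | Go | Better direction | Coherent as printed? |
|---|---|---|---|---|
| Meeting eligibility criteria | <20% | >50% | higher | yes |
| Acceptability | <30% | >60% or >70% | higher | yes |
| Loss to follow-up | <30% | >70% or >80% | lower | no |

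**The plan's own attrition figures**

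- Study 2 (Section 8.2.1): 54 per group are needed and 30% attrition is allowed. 54 / (1 − 0.30) = 77.1, rounded up to 78 per group, or 156 in total. The stated figure reproduces.
- Study 4 (Section 10.2.3): 168 in total with 20% attrition. 168 × (1 − 0.20) = 134.4, about 67 completers per group, and 67 / 0.80 = 83.75, rounded up to 84. The inflation is consistent.

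Both studies therefore treat these losses as acceptable. Under the printed rule, the planned 20% loss in Study 4 is below 30% and is a stop. The planned 30% loss in Study 2 lies exactly on the stop limit, and any better follow-up is a stop.

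**The same figures read as retention**

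Retaining more than 70% means losing less than 1 − 0.70 = 30%. Retaining more than 80% means losing less than 1 − 0.80 = 20%. These are the two allowances above. The layout also fits: in the acceptability item the stop value is single and the go value varies by study, and the third item has the same pattern.

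**The same figures with the order reversed**

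Here go would be a loss under 30% and stop a loss over 70% or 80%. The go limit agrees with the Study 2 allowance. A study would stop, however, only after losing more than 70% or 80% of its participants, against planned losses of 20% and 30%.

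**Illustration of scale**

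Section 12 does not say at which stage the rule is applied, so two assumptions are shown.

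- Applied to the main trials, a printed go (loss over 70%) leaves fewer than 156 × 0.30 = 46.8 participants in Study 2, against 108 required. In Study 4 it leaves fewer than 168 × 0.30 = 50.4, against about 134 planned completers. At a loss over 80% the figures are below 156 × 0.20 = 31.2 and 168 × 0.20 = 33.6.
- Applied to the Study 2 feasibility phase, with 20 participants per population, 20 × 0.30 = 6 and 20 × 0.70 = 14. Losing 5 of 20 would be a stop and losing 15 of 20 would meet the 70% go value.

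The direction is wrong under either assumption; only the counts differ.

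**The case against.** The best case on the other side has three parts.

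First, the retention reading is an inference. The label may be right and the order may simply not have been reversed for this item. There is some support for that: Section 12 cites reference 39 for the criteria, and Section 8.2.1 cites the same reference for the 30% attrition, so the 30% figure also makes sense as a loss. This stands as a second possibility. It is less likely, because the wording ties all three pairs to one order and because it implies a very late stop limit. It does not rescue the sentence, which is wrong as printed under either meaning.

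Second, a reader might infer that the rule would leave the main trials with about 47 of 156 or 50 of 168 participants and so badly underpowered. The documents do not support that as a consequence. Section 12 names no stage, the other two criteria look like feasibility measures, and the article says that every study includes a feasibility step. The counts show scale only.

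Third, the reversal is easy to see, and a team that planned for 20% or 30% attrition would be unlikely to halt a study for good follow-up. That is fair, and it lowers the practical risk. It does not make the stated threshold correct, and the two possible repairs lead to very different stop limits.

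**Conclusion.** The point holds as an error of direction in a stated decision rule. Read with its two companion criteria, the loss-to-follow-up item stops studies losing under 30% and passes those losing over 70% or 80%. This contradicts the 30% and 20% attrition that Studies 2 and 4 plan for. The conclusion rests only on the wording of Section 12 and those two allowances, and no power calculation is needed.

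Retention labelled as loss is the most likely explanation but is not established. A reader might also infer that 70% is the go value for Study 2 and 80% the go value for Study 4, because the complements match. Section 12 says only that the value differs between studies, and three of the five state no attrition allowance, so the assignment is for the sponsor to confirm. That the article does not list the values study by study is not itself a fault, since an article may leave this to the full protocols.

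**What to change.** Confirm with the investigators which meaning was intended, then correct the one sentence in Section 12. If retention was meant, replace the loss label with retention (follow-up completed), so that stop is below 30% retained and go is above 70% or 80% retained. If loss was meant, restate the thresholds in the correct direction for loss and check that the resulting stop limit is really the one wanted, given planned attrition of 20% to 30%. When making the correction, the sponsor should also confirm which go value applies to which study. The cost is one sentence; no sample size, outcome or analysis changes.

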To assess intervention effectiveness, campaign registrants will provide basic demographic information (i.e., age, sex, household characteristics, employment status, social media account, contact information) during registration (T0) and complete self-reported measures of their (a) stay-at-home motivation, intention and past-week behaviour; (b) threat and coping appraisals, measured using adapted instruments deployed in recent studies that tested PMT in the COVID-19 context [53,54]; and (c) depressive, anxiety and stress symptoms, as measured using the 21-item Depression Anxiety Stress Scale [57]. Follow-up data will be collected at the end of the active campaign (T1), and every 6 months thereafter until the end of the intervention (T2, T3, T4, T5). Invitations to complete the surveys will be delivered via the participants’ social media accounts, phone calls or email, based on the contact information provided at registration. Up to five attempts will be made before the participant is deemed lost to follow-up for that time point. To assess effectiveness, logic checking and missing data analysis will be performed. Missing data will be handled based on the degree and mechanism of missingness (i.e., deletion or imputation). Generalised estimating equations will be used to model within-subject longitudinal data to estimate population-average changes in stay-at-home motivation, intention and past-week behaviour; COVID-19 threat appraisal; stay-at-home coping appraisal; and psychological well-being (depression, anxiety, stress) across respondents over time. A minimum sample of 515 campaign registrants will be targeted to achieve 80% power and alpha of 0.0042 (to keep the overall type 1 error at 0.05 for 12 outcomes) with small intervention effect (Cohen’s d = 0.2) across timepoints for 6 repeat measures with an assumption of a first order autoregressive covariance pattern and a base correlation of 0.30.

## 10. Study 4

AI-driven Vaccine Communicator: The impact of a Web-based psychoeducation programme with a motivational AI-based digital assistant on COVID-19 vaccine hesitancy in Hong Kong’s population

To address the widespread hesitancy among HK residents toward COVID-19 vaccines, we will develop a Web-based psychoeducation programme, ‘AI-driven Vaccine Communicator,’ driven by artificial intelligence (AI) techniques based on the Vaccine Hesitancy Determinants Matrix Model and MI communication skills and concepts (theoretical underpinnings) [19].

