#### 11.2.5. Data Analysis

Descriptive statistics will be used to present all of the demographic, programme attendance and outcome data. Chi-square or independent sample *t*-tests (for categorical and interval data, respectively) will be used to identify the heterogeneity of demographic and baseline data in the two groups and settings. The effectiveness of the VRG-based educational intervention on the primary outcomes (the level of knowledge and practice, the bacterial loads and the detection rates of respiratory viruses) will be examined by linear mixed-effect modelling to compare changes in the primary outcome values of the intervention and control groups over time (from baseline to the two post-tests) on an intention-to-treat basis, using repeated-measures analysis of covariance, multivariate analysis of covariance and/or mixed modelling techniques.

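### Study 3 is sized at alpha 0.0042 per outcome to protect 12 outcomes, but the common rule in Section 12 calls any p below 0.05 significant and makes no exception for it

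*Protocol article*

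**What the plan says.** Two places in the protocol article bear on the threshold for Study 3.

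- **Section 9.2.2 (Study 3, end of the data and analysis text).** "A minimum sample of 515 campaign registrants will be targeted to achieve 80% power" at an "alpha of 0.0042 (to keep the overall type 1 error at 0.05 for 12 outcomes"). The other assumptions are a "small intervention effect (Cohen’s d = 0.2) across timepoints for 6 repeat measures" and a "first order autoregressive covariance pattern and a base correlation of 0.30". The same text plans generalised estimating equations for stay-at-home motivation, intention and past-week behaviour, threat appraisal, coping appraisal, and depression, anxiety and stress. It does not say at what level those tests will be judged.
- **Section 12.** Under the heading "Across All Studies, Other Common Elements Include", one sentence states that "All analyses will be performed using SPSS 26.0 software" and that a p "value < 0.05 will be considered statistically significant". No study is excepted and no adjustment for multiple outcomes is mentioned.

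**The concern.** The value 0.0042 appears only in the sample-size sentence. The only rule on how a p value will be read is the one in Section 12, and it gives 0.05. A Study 3 outcome with p between 0.0042 and 0.05 is a positive finding under Section 12, but not under the error control that Section 9.2.2 says the study was sized for.

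Three things are at stake. First, if Section 12 is followed, the overall 5% error rate promised for the 12 outcomes is lost. Second, the larger sample that the stricter alpha requires would buy protection that is never used. Third, while both values stand, the choice between them could be made after the results are known.

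**Working it through.** **Inputs.** Per-outcome alpha 0.0042, overall type 1 error 0.05, 12 outcomes, 515 registrants and 80% power (all Section 9.2.2); general threshold 0.05 (Section 12). The documents give no correlation between outcomes. I assume independence first, then exchangeable correlations from 0.1 to 0.9.

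**Step 1: reproduce the plan's alpha.** Bonferroni: 0.05 / 12 = 0.00417, which rounds to 0.0042 and matches. Šidák: 1 − 0.95^(1/12) = 0.00427, which rounds to 0.0043 and does not match. The plan's figure is a per-outcome Bonferroni level.

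**Step 2: family-wise error under independence, all nulls true.** The formula is 1 − (1 − α)^12.

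- At 0.05: 1 − 0.95^12 = 0.460, or 46%. The bound under any dependence is 12 × 0.05 = 0.60.
- At 0.0042: 1 − 0.9958^12 = 0.049, or 4.9%. The bound under any dependence is 12 × 0.0042 = 0.0504.

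**Step 3: correlated outcomes.** Twelve normal test statistics were simulated as Z_j = √ρ·C + √(1−ρ)·E_j, with 400,000 draws per value of ρ. A family-wise error is any |Z_j| above 1.960 (for 0.05) or above 2.863 (for 0.0042).

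| Assumed ρ | Each test at 0.05 | Each test at 0.0042 |
|---|---|---|
| 0 | 45.9% | 4.9% |
| 0.1 | 45.0% | 4.9% |
| 0.3 | 39.7% | 4.5% |
| 0.5 | 31.9% | 3.8% |
| 0.7 | 23.3% | 2.8% |
| 0.9 | 13.6% | 1.5% |

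Every value in the 0.05 column is well above 5%. Every value in the 0.0042 column is below it.

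**Step 4: what the stricter alpha costs in sample size.** For a test of a single contrast at 80% power (normal approximation), the ratio of required samples is (2.863 + 0.842)² / (1.960 + 0.842)² = 13.73 / 7.85 = 1.75. Then 515 / 1.75 is about 295, so about 220 of the 515 registrants are there for the stricter alpha. For a 5-degree-of-freedom test of a step change over the six time points, the required samples are 544 and 342, a ratio of 1.59. Then 515 / 1.59 is about 324, so about 191 registrants are. The plan does not state the contrast tested, so these are rough indications.

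**Step 5: can 12 be recovered?** The theoretical framework in Section 9 names six constructs: vulnerability, severity, self-efficacy, response efficacy, costs and rewards. Adding motivation, intention and past-week behaviour (3) and depression, anxiety and stress (3) gives 6 + 3 + 3 = 12.

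**The case against.** The strongest reply is that the two statements can be reconciled. Section 9.2.2 itself gives 0.05 as the overall level and 0.0042 as the per-outcome level. Section 12 is a general line on software and significance in a section of shared elements, and a statement specific to one study would ordinarily take precedence. This stands in part: the intended rule is probably 0.0042, and one clause settles it. But neither section says which prevails. Section 12 speaks of individual p values in all analyses, not of an overall level, and 0.0042 is never given as a decision rule. The detail of testing can be left to an analysis plan, but here the article states two levels that disagree.

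A second reply is that 46% is a worst-looking figure. That also stands in part. Depression, anxiety and stress come from one scale, and the theory links appraisals to motivation and intention, so independence is implausible. The range in the table is the fairer statement, and all of it exceeds 5%.

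Three stronger readings are tempting, and the documents do not support them.

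- **The family of 12 is unfounded, because the analysis sentence names only eight outcomes.** Eight is the count if each appraisal is one outcome. Split into the constructs in Section 9, the total is 12. The article does not list them, so this is an inference, but it makes listing them a clarification and not the repair of an error.
- **Study 5 has the same fault, because it names "primary outcomes (the level of knowledge and practice, the bacterial loads and the detection rates of respiratory viruses") and tests them at 0.05.** Nothing in the article promises control across those outcomes, and Section 11.2.1 sizes that study at 0.05, in line with Section 12. There is no contradiction, and handling of multiplicity is something an article may leave to the full plan. Imposing Holm across four outcomes would also cost power: the smallest p would face 0.0125, where a test with 80% power at 0.05 has about 62% (2.80 − 2.50 = 0.30 on the normal scale).
- **The 515 is wrong.** It was not reproduced: single-contrast variants at 0.0042 and 80% power give about 480 (baseline against T1), 615 (linear slope) and 684 (baseline against the last visit). The tested contrast is not stated, so this shows no error, and the point does not depend on it.

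**Conclusion.** The point holds for Study 3 alone. The threshold stated for its analyses (0.05) contradicts the per-outcome alpha used to size it (0.0042). If Section 12 is followed, family-wise error is about 46% with 12 independent outcomes and all nulls true, and about 14% to 45% for assumed exchangeable correlations of 0.9 to 0.1, against the 5% promised. At 0.0042 it is about 4.9% or lower. The correlations are assumptions, and the figures apply only if Section 12 is taken at its word.

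This should be fixed, but it is not a critical flaw. The intended level can be inferred, the sample size already allows for it, and the effectiveness assessment is a single-group pretest–posttest comparison of voluntary registrants.

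**What to change.** 1. In Section 12, qualify the threshold. For example: *a p value below 0.05 is considered significant unless a study states otherwise; Study 3's 12 outcomes are each judged at 0.0042, or by Holm's procedure at an overall level of 0.05.*
2. In Section 9.2.2, list the 12 outcomes that make up the family. If they are the six theory constructs plus motivation, intention, past-week behaviour, depression, anxiety and stress, say so.

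The cost is a clause and a list. The target of 515 does not change, because it already assumes 0.0042. Holm's first step is the same 0.05/12 and its later steps are less strict, so it needs no more participants either. Study 3 gives up only the ability to call a p value between 0.0042 and 0.05 significant (under Holm, only where the later steps do not allow it), which its own sizing statement already implies. The change should be made before outcome data are examined.

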## 13. Ethics Considerations

Ethics approvals for each study has already been obtained from the Institutional Review Board of the Hong Kong Polytechnic University. Online or face-to-face written informed consent (and accent from minors) will be obtained from all participants before data collection. Agreements from the recruitment sites to carry out the research and co-participate will be obtained too. Participation is entirely voluntary, and subjects can withdraw from the research at any time without any penalty. Participants’ identities and data will be protected by maintaining anonymity and confidentiality. Only authorized personnel will be able to access the data for analysis. Mental health service information will be integrated into the intervention if participants feel anxious or have other emotive reactions/needs. In one study where employers are involved as subject recruiters, more specific processes have been established to prevent coercion and exertion of power. Study team members and collaborators will strictly abide by all principles of research ethics, protection of participant anonymity and their data.

## 14. Implications

The proposed studies are expected to have direct and positive impacts on the HK community and to reduce the risk of COVID-19 transmission by improving preventative and early detection measures, increasing compliance with and improving the experience with social distancing measures, promoting the uptake of vaccines and increasing eHealth literacy related to COVID-19. The results of these studies will also inform the planning and preparation of responses to future pandemics. Decreased infection rates are expected due to improved preventative behaviours and increased vaccine uptake. The long-term sustainability of the approach will be achieved through the CBPR model processes.

